### **Myfortic®**

In both treatment groups, Myfortic® should be given according to the "loading dose" regimen: 2880 mg/day during week 1 to 2, 2160 mg/day in week 3 to 6 and then maintained at 1440 mg/day in week 7 to 24, if tolerated.

In case of leukopenia (leukocyte count  $<2,500/\text{mm}^3$ ), neutropenia (neutrophil count  $<1,500/\text{mm}^3$ ), or anemia, Myfortic® medication doses may be reduced at the discretion of the investigator or eliminated completely until the event resolves. Furthermore, for any other moderate/severe AE which in the opinion of the investigator warrants a dose reduction or temporary interruption of the medication, this will be allowed. However, the Myfortic® medication should be restarted once the AE has resolved or returned to an acceptable grading (see instructions given in [Appendix 4](#)).

If Myfortic® medication is interrupted for safety related considerations for more than 2 consecutive weeks or more than 4 cumulative weeks within the 6 months study treatment, discontinuation of the medication should be considered and the patient should be withdrawn from the study. Appropriate information needs to be recorded on the Dosage Administration CRF.

The Month 6 assessments will be performed and documented for all patients who are withdrawn prematurely from the treatment at timepoint of discontinuation.

### **Oral corticosteroids**

Oral corticosteroids will be given at a minimum dose of 5 mg prednisolon or equivalent during the first two weeks post transplantation. If possible, it should remain stable during these two weeks. However, dose adjustments for medically indicated reasons will be possible.

All immunosuppressive medication, with single dose, unit, frequency, route of administration, indication, start and end dates will be recorded in the Immunosuppressive Therapies CRF. Only approved but no investigational drugs are permitted.

### **6.5.3 Rescue medication**

#### **Treatment for acute rejection episodes**

A core biopsy must be obtained for all suspected cases of acute rejection. Such biopsies are to be performed prior to or within 24 hours after the start of anti-rejection therapy. Whenever possible, anti-rejection therapy should be postponed until a histological diagnosis of rejection is confirmed. These biopsies will be read locally at the center, and assessed according to Banff 07 criteria (see [Appendix 6](#)).

Acute rejection should be treated with methylprednisolone intravenously. The recommended dose is 500 – 1000 mg for three days. In cases of Grade III/vascular rejection, the administration of ATG/OKT3 or high doses of i.v. Immunoglobulin is allowed as first line treatment. Plasmapheresis is also allowed in these patients. Patients receiving such therapy may interrupt study medication during that period.

A **steroid-resistant acute rejection** episode will be defined when no stabilization or improvement of creatinine is seen within five days after initiation of methylprednisolone, when the patient has received at least 4 bolus injections with a minimum of 250 mg/bolus, or a total minimum of 1.5 g of methylprednisolone. For such steroid-resistant rejections, antilymphocyte therapy may be initiated at the appropriate dose for 7 – 14 days. However, if there is inadequate response to a full course of steroids and initiation of antilymphocyte therapy is delayed more than 10 days from the biopsy-confirming acute rejection, a repeat biopsy should be performed to confirm ongoing rejection prior to initiating antilymphocyte antibody therapy.

Patients suffering rejection  $\leq$  BANFF 1A should be randomized and treated according to immunosuppressive regimen given in the study protocol.

#### **Infection prophylaxis**

Prophylactic treatment for Cytomegalovirus (CMV) for high risk patients (a CMV positive donor organ transplanted into a CMV negative recipient) is strongly

recommended. Treatment will be at the investigator's discretion per standard practice of the individual centers.

All patients may receive prophylactic treatment for *Pneumocystis Carinii* Pneumonia (PCP) with trimethoprim/sulfamethoxazole (e.g. Bactrim® or Cotrim®) according to local practice. Duration and dosage depend on the discretion of the investigator. Aerosolized pentamidine or dapsone may be administered to patients unable to tolerate oral formulations.

### **Treatment of hyperlipidemia**

Lipid lowering medications (e.g., fluvastatin, Lescol®) are to be administered for patients with increased LDL-cholesterol and triglyceride levels following the National Cholesterol Educating Program (NCEP) guidelines ([Appendix 5](#)). Lipid lowering medications should be maximized prior to reduction of Certican®. If the elevation of cholesterol and/or triglyceride levels persists, the dosing of Certican® will be adjusted following the recommendations in [Appendix 4](#).

When HMG-CoA reductase inhibitors are used concomitantly with gemfibrozil (and probably other fibrates), cyclosporine or erythromycin, myopathy and rhabdomyolysis have been reported. Caution is advised if the use of such combinations is deemed necessary.

#### **6.5.4 Other concomitant treatment**

The investigator should instruct the patient to notify the study site about any new medications he/she takes after the start of the study treatment. All medications (other than study treatment) and significant non-drug therapies (including physical therapy and blood transfusions) administered after the patient starts study treatment must be listed on the "Concomitant medications/Significant non-drug therapies after start of study drug" CRF. If required for an AE, such concomitant medication should be cross-referenced on the AE CRF under "action taken", appropriately coded for "concomitant medication taken".

Inducers of CYP3A4 (e.g. rifampin, carbamazepine, phenytoin, and barbiturates have been shown or have the potential to decrease exposure to Certican®. If these drugs are necessary, Certican® doses may have to be increased. Potent inhibitors of CYP3A4 such as ketoconazole, itraconazole and fluconazole should be avoided while the patient is on study medication. Certican® has the potential to increase the exposure to terfenadine, astemizole and cisapride; hence these drugs should be avoided. In vitro data suggested that Certican® may have the potential to interact with quinidine, fluoxetine and paroxetine, and alternative medications should be considered. Since the potential for drug interaction with digoxin has not been evaluated, patients on digoxin should have periodic measurement of digoxin levels.

The concomitant administration of nephrotoxic drugs (e.g., aminoglycosides, NSAIDs) and drugs known to interfere with cyclosporine pharmacokinetics (i.e., ketoconazole, erythromycin, phenytoin, barbiturates, carbamazepine, diltiazem, verapamil, rifampin) should be associated with a careful monitoring of renal function

and cyclosporine blood trough levels. In addition, drugs known to interfere with Certican® or Myfortic® should be avoided (see [Appendix 3](#) for possible drug interactions).

#### 6.5.5 Study drug discontinuation

In case of a platelet count  $<75,000/\text{mm}^3$ , a leukocyte count  $<2,500/\text{mm}^3$  or a neutrophil count  $<1,500/\text{mm}^3$ , at the discretion of the investigator, Myfortic® medication dose may be reduced by half, or eliminated completely until the event resolves. In case of dose reduction, Myfortic® should be reduced according to the guidelines given in [Appendix 4](#). In the CNI-free group, Certican® should be continued on a stable dose level and reduced only if the symptoms do not respond to the reduction of the Myfortic® dosage.

In case of elevated cholesterol and/or triglyceride levels, lipid lowering medications should be maximized. If the elevation persists, the dosing of Certican® should be adjusted following the recommendations given in [Appendix 4](#).

Dose reduction may be performed for those patients with other moderate/severe AEs according to the investigators' judgment. Also in these cases, the medication doses can be reduced by half or interrupted completely until event resolves.

If the Myfortic® or Certican® medication is interrupted for more than 2 consecutive weeks or more than 4 cumulative weeks within the 6 months study treatment, discontinuation of the respective medication should be considered and the patient withdrawn from the study.

Patients who discontinue study treatment before completing the 6-month period should be scheduled for a the end of study visit as soon as possible, at which time all of the assessments listed for the end of study visit (Visit 6, Month 6) will be performed.

All patients who discontinue study drug, including those who refuse to return for a final visit, will be contacted for safety evaluations during the 30 days following the last dose of study drug taken.

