#### **Certican®**

Because Certican® is the mainstay of immunosuppression in the CNI-free group, Certican® dose should be continued on a stable level according to trough levels. Therefore reduction or elimination of Myfortic® should be considered first (step 1) before adjusting the Certican® dose (step 2).

Steroids could be added to the immunosuppressive regimen if necessary (step 3). In case of not achieving sufficient immunosuppression Sandimmun® Optoral could be added to the IS treatment in the Certican®-group (step 4).

Target therapeutic ranges for Certican® (everolimus) whole blood trough levels after CNI-removal should be 5 to 10 ng/mL.

Dose adjustments may be performed if Certican® (everolimus) whole blood trough levels outside the target range are measured. Dose adjustments of Certican® should be monitored 7 days later by a measurement of the everolimus blood trough level.

In both renal and heart transplantation, everolimus trough concentrations  $\leq 3$  ng/mL were associated with a significantly lower protection from acute rejection compared with trough levels  $> 3$  ng/mL. Although hyperlipidemias were common over the full exposure range, they responded to corticosteroid dose reduction, dietary management, and lipid-lowering therapies, and were, therefore, not dose-limiting. The incidence of leukocytopenia did not show any exposure-response relationship to everolimus trough concentrations. The incidence of notable thrombocytopenia ( $< 100 \times 10^9/L$ ) increased with Certican® exposure; however, the incidence of clinically meaningful platelet reductions ( $< 75 \times 10^9/L$ ) was generally low.

When Certican® is used with conventionally dosed CsA, the lower therapeutic concentration was 3 ng/mL (Kovarik et al., 2001, 2002b; Vitko et al., 2004). For safety reasons, therefore, a higher lower limit seems necessary, when CsA is discontinued. This was the rationale to increase the lower limit to 5 ng/mL after withdrawal of Sandimmun® Optoral. A more precise upper therapeutic limit could not be defined. There is, however, limited clinical experience that doses causing concentrations  $> 8$  ng/mL may lead to an increased frequency of side effects (Kovarik et al., 2001, 2002b, 2002c; Vitko et al., 2004). Certican® (everolimus) trough levels  $> 12$  ng/mL should be avoided.

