If Certican® medication is interrupted for safety related considerations for more than 14 consecutive days within the 6 months study treatment (or cumulative for more than 4 weeks), discontinuation of the medication should be considered and the patient should be withdrawn from the study. Appropriate information needs to be recorded on the Dosage Administration CRF.

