## Appendix 4: Dose Reduction of Certican® and Myfortic®

Dose reduction or temporary interruption may be performed for Myfortic® or Certican®. However, Certican® should be continued on a stable dose level, if possible, and reduced or interrupted only if the symptoms do not respond to the reduction of the Myfortic® dosage.

Implementation of dose reduction will be based on thrombocytopenia, leukopenia, neutropenia, hyperscholesterolemia, hypertriglyceridemia, or other adverse events which are suspected to be related to study medication, and in the opinion of the investigator, are clinically warranted. The following guidelines should be used for both dose reduction and restarting or increasing the dose of study medication back to original levels.

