### Dose Reduction Guidelines

#### Platelets

- platelet count < 100,000/mm^3    dose **may** be reduced at the discretion of the investigator
- platelet count < 75,000/mm^3    a second dose reduction should be **considered**
- platelet count < 50,000/mm^3    **MANDATORY** interruption of medication

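### Section 6.5.5, and Section 6.5.2 for neutrophils, leave stopping Myfortic optional at counts where Appendix 4 makes interruption mandatory

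*Protocol*

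**What the plan says.** Three places in the Protocol govern Myfortic when blood counts fall.

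- **Section 6.5.5 (Study drug discontinuation).** At platelets below 75,000/mm³, leukocytes below 2,500/mm³ or neutrophils below 1,500/mm³, the investigator decides, and the Myfortic "medication dose may be reduced by half, or eliminated completely until the event resolves". The next sentence says that, where the dose is reduced, the Appendix 4 guidelines apply.
- **Section 6.5.2 (Permitted study drug adjustments, Myfortic).** For leukopenia, neutropenia (below 1,500/mm³) or anemia, Myfortic "medication doses may be reduced at the discretion of the investigator or eliminated completely until the event resolves". It gives no platelet threshold. Its pointer to Appendix 4 is attached to the sentence on restarting Myfortic.
- **Appendix 4.** At platelets below 50,000/mm³ the instruction is "MANDATORY interruption of medication". At ANC below 1,000/mm³, interruption of study medication is likewise mandatory. Neither line names the drug.

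On Certican, Section 6.5.5 says that in the CNI-free group it "should be continued on a stable dose level and reduced only if the symptoms do not respond to the reduction of the Myfortic" dosage. The opening of Appendix 4 says that it "should be continued on a stable dose level, if possible, and reduced or interrupted only if the symptoms do not respond" to reduction of Myfortic.

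**The concern.** The discretionary rule in the main text has no lower bound, so it covers the same patients as the mandatory rule in the appendix. At an ANC of 900/mm³, for example, Section 6.5.5 lists halving Myfortic as an acceptable choice, while Appendix 4 requires an interruption. The permissive wording stands in the main-text section that deals with stopping study drug, and the Protocol does not say which text prevails.

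The stake is safety in a few patients. A site working from the main text could keep a patient on reduced Myfortic at a count where the sponsor has decided that the drug must stop. Monitors would also lack a clear basis for deciding whether that site had deviated from the protocol.

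**Working it through.** The point rests on no sample size, power or error-rate figure, so the check is a comparison of the rules.

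**1. Do the thresholds overlap?** Platelets below 50,000 lie inside platelets below 75,000, and ANC below 1,000 lies inside neutrophils below 1,500. Every patient who meets a mandatory tier therefore also meets the Section 6.5.5 condition.

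**2. What does each text require?**

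| Count (/mm³) | Section 6.5.5 | Section 6.5.2, Myfortic | Appendix 4 |
|---|---|---|---|
| Platelets 50,000 to <75,000 | may halve or stop | no platelet rule | second reduction to be considered |
| Platelets <50,000 | may halve or stop | no platelet rule | interruption mandatory |
| ANC 1,000 to <1,500 | may halve or stop | may reduce or stop | reduction to be considered |
| ANC <1,000 | may halve or stop | may reduce or stop | interruption mandatory |

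The texts agree in the first and third rows and conflict in the second and fourth. Leukocytes show no such conflict, because Appendix 4 leaves reduction discretionary there and sets no mandatory stop.

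**3. Where does halving fall on the Appendix 4 scale?** The Myfortic step table gives:

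- maintenance: 2 × 360 mg twice daily = 1,440 mg/day;
- first reduction: (360 + 180) mg twice daily = 1,080 mg/day;
- second reduction: 2 × 180 mg twice daily = 720 mg/day.

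Half of 1,440 is 720 mg/day, so halving from maintenance is the second reduction. For platelets, Appendix 4 attaches that step to counts below 75,000 and requires interruption below 50,000. Halving at the lowest tier is therefore one step short of what the appendix demands.

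**4. Which drug do the mandatory lines mean?** The Myfortic-first order in Sections 6.5.2 and 6.5.5 and in the opening of Appendix 4, together with a step table that lists only Myfortic, points to Myfortic. The term *study medication* does not establish this by itself. The lipid part of the same appendix uses it for the drug that Section 6.5.3 identifies as Certican ("the dosing of Certican® will be adjusted following the recommendations in" Appendix 4). Naming Myfortic in the count-based lines would remove the doubt.

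**The case against.** The best defence is that Section 6.5.5 is not cut off from the appendix. Halving is a dose reduction, and the section sends dose reductions to Appendix 4, where the platelet stop stands under the heading for dose reduction guidelines and the ANC stop follows in the same appendix. A site that eliminates Myfortic complies anyway. A general rule in the body with stricter tiers in the appendix it cites is a common layout.

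Much of this stands, and it makes the conflict milder. It does not remove it: halving remains a listed choice at these counts, and no order of precedence is stated. The Section 6.5.2 pointer helps less, because it concerns restarting.

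Two stronger readings are tempting, and the documents do not support them.

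- **That Appendix 4 is silent on Certican, so a mandatory stop could leave CNI-free patients without oral maintenance.** Its opening covers interruption of Certican expressly: continue if possible, and interrupt only if Myfortic reduction does not work. No exception is stated for the lowest tiers. Section 6.5.2 also offers steroids and then Sandimmun Optoral as further steps.
- **That the restart waits would push patients towards the withdrawal threshold, set for Certican "interrupted for safety related considerations for more than 14 consecutive days within the 6 months study treatment".** The lowest, mid and full restart doses match the Myfortic table, a note at the end of the lipid guidance gives discretion over the dose at restart, and passing the threshold only means that discontinuation should be considered. No count of days off Certican can be built on this.

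**Conclusion.** The point holds as a minor patient-safety inconsistency. At platelets below 50,000/mm³ (Section 6.5.5) and ANC below 1,000/mm³ (Sections 6.5.5 and 6.5.2), the main text allows a reduction where Appendix 4 requires a stop. It concerns Myfortic, and so both arms of the planned 244 patients.

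Few patients are likely to be affected. The Protocol gives no incidence for either tier. Section 6.5.2 describes platelet falls below 75 × 10⁹/L under Certican as generally uncommon, and platelets below 75,000/mm³ or ANC below 1,500/mm³ at Baseline visit 2 exclude a patient from randomization. The primary GFR comparison, by assigned treatment, does not change.

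The conclusion assumes that the mandatory lines apply at least to Myfortic, which the Myfortic-first order supports, and that some sites will act on the main text alone.

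**What to change.** Make three wording changes.

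1. **Section 6.5.5:** add that Myfortic must be interrupted at platelets below 50,000/mm³ or ANC below 1,000/mm³, as set out in Appendix 4, and that the option to halve applies only above those counts.
2. **Section 6.5.2, Myfortic:** add the same statement for ANC below 1,000/mm³.
3. **Appendix 4:** name Myfortic in the two mandatory lines, and add that Certican follows the rule at the head of the appendix (continued if possible, interrupted only if counts do not respond to Myfortic reduction).

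The cost is amendment text and a notice to sites, with no extra visits, patients or analyses. Investigators lose discretion only at the two tiers where Appendix 4 already removes it.

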#### 6.5.6 Premature patient withdrawal from study treatment

Patients *may* voluntarily withdraw from study treatment or study treatment may be discontinued at the discretion of the investigator at any time.

Patients must be withdrawn prematurely from the study treatment if any of the following occur:

- premature discontinuation of study drug (see [Section 6.5.5](#))
- graft loss

- severe acute rejection (see [Section 6.5.3](#), first line rescue medication) requiring change in baseline immunosuppressive therapy according to this protocol
- occurrence or detection of severe medical disorder jeopardizing the life of the patient in the immediate future

If such premature withdrawal from study treatment occurs, or if the patient fails to return for visits, the investigator must determine the primary reason for a patient's premature withdrawal from the study and record this information on the Study Completion CRF.

Patients may be withdrawn from the study treatment prematurely at the investigator's discretion for one of the following reasons:

1. adverse event(s)
2. abnormal laboratory value(s)
3. abnormal test procedure result(s)
4. unsatisfactory therapeutic effect (e.g. severe rejection)
5. protocol violation
6. administrative problems
7. patient's condition no longer requires study treatment

For patients who are lost to follow-up, the investigator should show "due diligence" by documenting in the source documents steps taken to contact the patient, e.g., dates of telephone calls, registered letters, etc.

Patients who discontinue participation in the trial for any reason will not be replaced.

All patients who prematurely discontinue study treatment will not be considered as withdrawn from the study and will be asked to attend the end of study visit (at time point of discontinuation).

The End of Study CRF should be completed at month 6 or earlier if the patient can no longer be followed, e.g., due to death, withdrawal of consent, or loss to follow-up.

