## **Glossary of terms**

|                              |                                                                                                                                                                                                                                      |
|------------------------------|--------------------------------------------------------------------------------------------------------------------------------------------------------------------------------------------------------------------------------------|
| Assessment                   | A procedure used to generate data required by the study                                                                                                                                                                              |
| Control; control drug        | A study drug used as a comparator to reduce assessment bias, preserve blinding of investigational drug, assess internal study validity, and/or evaluate comparative effects of the investigational drug                              |
| Enrollment                   | Point/time of patient entry into the study; the point at which informed consent must be obtained (i.e., prior to starting any of the procedures described in the protocol)                                                           |
| Investigational drug         | The study drug whose properties are being tested in the study; this definition is consistent with US CFR 21 Section 312.3 and is synonymous with "investigational new drug."                                                         |
| Patient number               | A unique identifier assigned to each patient who enrolls in the study                                                                                                                                                                |
| Premature patient withdrawal | Point/time when the patient exits from the study prior to the planned completion of all study drug administration and assessments; at this time all study drug administration is discontinued and no further assessments are planned |
| Randomization number         | A unique identifier assigned to each randomized patient, corresponding to a specific treatment group assignment                                                                                                                      |

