| Rejection episodes                           | ← as necessary → |   |                      |                |    |    |                  |
| Renal biopsy                                 | ← as necessary → |   |                      |                |    |    |                  |
| Infections                                   | ← as necessary → |   |                      |                |    |    |                  |
| Tumour                                       | ← as necessary → |   |                      |                |    |    |                  |
| AEs                                          | ← as necessary → |   |                      |                |    |    |                  |
| SAEs                                         | ← as necessary → |   |                      |                |    |    |                  |
| Comments                                     | ← as necessary → |   |                      |                |    |    |                  |
| Concomitant therapy                          | ← as necessary → |   |                      |                |    |    |                  |
| Immunosuppressive therapy                    | ← as necessary → |   |                      |                |    |    |                  |
| End of treatment / End of study  |                  |   |                      |                |    |    | x                |

BL: Baseline visit 1: prior to transplantation  
EOS: End of Study

BL2: Baseline visit 2 : day of randomization

- 1) Visit 1 (BL ) is to be performed prior to transplantation
- 2) At end of study (Week 24 post Tx) or at the time of early discontinuation
- 3) Blood level control on Day 7 ± 2 after randomization
- 4) Optional
- 5) To be assessed only if Sandimmun® Optoral or Certican® are administered at that visit. Certican®-troughlevels will be determined locally.
- 6) Optional – if part of center standard procedure – control biopsies may be taken only at indicated time points

Patients should be seen for all visits on the designated day or as close to it as possible. Visit 3 (Week 7 – BL2) may be performed within a time window of week 7 and week 8.

### Visit 1 (day 0 / Week 0) – Baseline visit 1

The Baseline visit 1 assessment is to be performed prior to transplantation, i.e. within 24 hours before surgery.

1. Patient signs informed consent
2. Patient's eligibility for the study according to in- and exclusion criteria will be checked

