### **Visit 7 (Week 24) – End of Treatment**

In case of early discontinuation, Week 24 assessments need to be performed

- as soon as possible after treatment discontinuation
  - additionally at the originally planned timepoint, i.e. 6 months after transplantation
1. A complete physical examination will be performed
  2. (Changes in) smoking status will be recorded and the cardiovascular risk (Framingham Score, see [Appendix 7](#)) will be calculated.
  3. Vital signs will be measured.
  4. Returned study medication will be counted.
  5. Venous blood will be drawn for measurement of hematology and biochemistry (complete program).
  6. An oral glucose tolerance test (OGTT) with a concomitant insulin measurement will be performed.
  7. Venous blood will be drawn for measurement of viral serology

8. Venous blood will be drawn for measurement of
  - cyclosporine C0h-level (Control group)
  - Certican® (everolimus) trough level -local determination- (Certican® group)
9. Urinalysis will be performed, the Glomerular Filtration Rate (GFR) will be assessed.
10. Changes in concomitant medications / significant non-drug therapies will be recorded.
11. Changes in immunosuppressive medication (including study drug dosage) will be recorded.
12. Information on rejection episodes, renal biopsies, hospitalization, infections, and other (S)AEs that occurred since the last visit will be recorded.
13. Optionally – if part of center standard procedure – a control biopsy may be taken. Control biopsies should be assessed by a central nephropathologist and should only prompt therapy in cases of severe rejection, infection or toxicity. In order to avoid any bias, which could interfere with the objectives of the study, investigators should be kept blinded until completion of the study.
14. End of Study / End of Treatment information will be obtained.

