#### 10.4.1 Variable

The primary variable for assessment of renal function is the glomerular filtration rate (GFR) at Month 6, as assessed by the Cockcroft-Gault method (recalculated values, see [Section 7.5](#)).

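### The protocol contradicts itself on whether patients who stop treatment early are measured again at Month 6, so their primary GFR may go unmeasured or be taken early

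*Protocol*

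**What the plan says.** Section 10.4.1 fixes the time point: "The primary variable for assessment of renal function is the glomerular filtration rate (GFR) at Month 6". Section 10.1 analyzes every randomized patient in the assigned arm, and Section 10.4.4 keeps patients whose treatment changes in that arm.

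On when early stoppers are assessed:

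- Section 6.5.2 (Myfortic): "The Month 6 assessments will be performed and documented for all patients who are withdrawn prematurely from the treatment at timepoint of discontinuation".
- Section 6.5.5 asks for a prompt final visit, at which "all of the assessments listed for the end of study visit (Visit 6, Month 6) will be performed". No later visit is named.
- Section 6.5.6: such patients "will be asked to attend the end of study visit (at time point of discontinuation").
- Table 7-1, footnote 2: "At end of study (Week 24 post Tx) or at the time of early discontinuation".
- Section 7, Visit 7: assessments promptly after stopping and "additionally at the originally planned timepoint, i.e. 6 months after transplantation".

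On whether they remain in the study:

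- Section 6.5.5, after a prolonged interruption: "discontinuation of the respective medication should be considered and the patient withdrawn from the study". The Certican, Sandimmun Optoral and Myfortic paragraphs of Section 6.5.2 say much the same.
- The glossary, on premature patient withdrawal: "at this time all study drug administration is discontinued and no further assessments are planned". It defines study drug discontinuation separately and says that the two may or may not coincide.
- Section 6.5.6 says that patients who stop treatment early still count as in the study. It places the End of Study form at Month 6 unless the patient can no longer be followed.

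**The concern.** An as-randomized comparison at a fixed time needs the outcome at that time from patients who have left their assigned treatment. Section 6.5.6 lists adverse events, severe rejection and graft loss among the reasons for stopping, so their renal function may well differ from that of patients who continue.

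The protocol gives sites two incompatible instructions for these patients. Two of the 8 to 12 centers could treat identical patients alike and still supply different data, one a Week 24 GFR and the other only an earlier value.

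The missing-data plan does not settle this. Section 10.4.3 triggers multiple imputation when a patient discontinues the study, which is the status on which the protocol disagrees with itself. If a discontinuation-time assessment is documented as the Month 6 assessment, as Section 6.5.2 can be read to ask, the value does not look missing. Neither the imputation nor the last-observation analysis would then act on it, and the repeated-measures model could take it as a Month 6 value.

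**Working it through.** **Step 1. Follow one patient through each rule.** Take a randomized patient who stops treatment around Week 12, is alive and still consents.

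| Place | Assessment when treatment stops | Assessment at Week 24 | Status |
|---|---|---|---|
| 6.5.2 (Myfortic) | Yes, described as the Month 6 assessments | None named | Out of the study if the interruption was prolonged |
| 6.5.5 | Yes, promptly | None named | Out of the study if the interruption was prolonged |
| 6.5.6 | Yes | No visit named, but the End of Study form is due then | In the study |
| Table 7-1, footnote 2 | One or the other | One or the other | Not stated |
| Section 7, Visit 7 | Yes | Yes | In the study by implication |

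Only the Visit 7 text states outright that a Week 24 measurement is taken. Section 6.5.6 is compatible with it. Sections 6.5.2 and 6.5.5 and the footnote, taken literally, can be followed without one. Where the glossary's definition of withdrawal applies, they lead to none.

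**Step 2. Visit number.** Section 6.5.5, the opening of Section 10 and the data analysis part of the synopsis call the Month 6 visit Visit 6. In Tables 4-1 and 7-1 and in the visit descriptions, Visit 6 is Week 18 and Week 24 is Visit 7.

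**Step 3. The plan's own figures (Section 10.7).** The planned difference is 60 − 52 = 8 ml/min, with standard deviation 19, two-sided 5% level and 135 and 68 evaluable patients. The noncentral t distribution gives 80.5% power, so the stated 80% reproduces. The correction proposed here changes none of these inputs; the 8 ml/min serves only as a yardstick.

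**Step 4. Size of a possible bias.** Let f be the share of an arm whose Month 6 value is replaced (early or imputed), and D the average of the value used minus the true Month 6 value. The difference in means, Certican minus control, shifts by

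shift = f(Certican) × D(Certican) − f(control) × D(control).

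The protocol states neither f nor D, so these are assumed ranges:

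- Certican only, f = 10%, D = 5: 0.10 × 5 = 0.5 ml/min, or 0.5/8 = 6% of the planned difference.
- Certican only, f = 20%, D = 10: 0.20 × 10 = 2.0 ml/min, or 25%.
- Certican only, f = 30%, D = 15: 0.30 × 15 = 4.5 ml/min, or 56%.
- f = 20% Certican and 10% control, D = 10 in both: (0.20 − 0.10) × 10 = 1.0 ml/min.
- Equal f and equal D in both arms: 0.
- Certican only, f = 20%, D = −10 (value taken at a low point): −2.0 ml/min.

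**The case against.** The strongest reply is that the Visit 7 text is the operative visit instruction and expressly requires the second assessment. Section 6.5.6 supports it by keeping stoppers in the study and placing the End of Study form at Month 6. The glossary already separates stopping drug from leaving the study. Section 10 analyzes all randomized patients as randomized and imputes what is missing. This stands to the extent that a site applying the Visit 7 text obtains the right value, so a reader who infers that the Month 6 GFR of stoppers will be lost goes too far. It does not remove the contradiction, because other sections give a different instruction and the footnote sits under the assessment schedule itself.

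A second reply is that nothing shown maps the discontinuation value to the Month 6 variable in the analysis. CRF pages are not shown, and visit mapping commonly belongs in the SAP. This also stands: the protocol creates the opening for such a mapping but does not prescribe it.

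A third reply concerns direction. A reader might infer that the flaw favors Certican, by 8 ml/min times the share who stop, on the view that an early on-drug gain is later lost. That requires every stopper to have the full 8 ml/min gain when stopping, to lose all of it by Month 6, and controls to be unaffected. The documents establish none of this. A creatinine taken during rejection or toxicity may be worse than at Month 6, which would penalize Certican. Section 10.4.4 itself expects GFR to improve on Certican and regards carrying earlier values forward as conservative.

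**Conclusion.** The point holds as an internal contradiction that bears on the primary endpoint. The protocol gives conflicting rules on when patients who stop treatment are assessed and on whether they remain in the study. Depending on the section a site follows, their Month 6 GFR may be unmeasured, or a discontinuation-time value may be documented as the Month 6 assessment.

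The size cannot be fixed from the protocol. With error in the Certican arm only, assumed shares of 10-30% and errors of 5-15 ml/min move the difference by 0.5 to 4.5 ml/min in either direction, against a planned 8. With equal shares and equal errors in both arms the shift is zero. The documents support neither a certain loss of the data nor a bias in a known direction.

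**What to change.** Reconcile Sections 6.5.2, 6.5.5 and 6.5.6 and Table 7-1 footnote 2 with the Visit 7 text:

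- Every randomized patient who is alive and still consenting has serum creatinine and weight, both needed for Cockcroft-Gault, measured at Week 24 after transplantation, whatever treatment is then being taken.
- The discontinuation visit gets its own label and is not used as the Month 6 value.
- The primary ANCOVA uses the observed Week 24 value, with multiple imputation only where that value is truly missing.
- The glossary's two terms, study drug discontinuation and premature patient withdrawal, are used consistently. The sections that describe study withdrawal after a prolonged interruption must be reconciled with Section 6.5.6. This concerns follow-up only and need not alter when treatment is stopped.
- Visit 6 becomes Visit 7 wherever Week 24 or Month 6 is meant: the synopsis (data analysis), Section 6.5.5 and the opening of Section 10.

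The cost is a wording amendment and a reminder to sites. No visit is added, because the Visit 7 text already requires it, and no sample size input changes. A Week 24 creatinine that was not drawn cannot be recovered later, so the change should reach sites before more patients stop treatment.
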